## Methods

### Trial design

This clinical feasibility trial protocol is designed as a waitlist-controlled 6-week home-based AR gait-and-balance exergaming intervention, in which the type of AR glasses (Magic Leap 2, HoloLens 2) will be counterbalanced over participants (Table 1). All participants will start with a 6-week waitlist period, followed by the 6-week home-based AR therapeutic gait-and-balance exergaming intervention Reality DTx^®^. Baseline (t0), pre-intervention (t1), and post-intervention (t2) repeated measurements will be conducted to compare within-participant Reality DTx^®^ intervention effects against usual care (i.e. does t2–t1 differ from t1–t0?) while controlling for potential learning effects in outcomes over repeated measurements (i.e. does t1–t0 systematically deviate from 0?). Between-group comparisons will be performed to evaluate potential AR glasses superiority (i.e. does t2–t1 differ between HoloLens 2 and Magic Leap 2 subgroups)? Feasibility of the Reality DTx^®^ intervention will be examined in terms of safety, adherence, and user experience (i.e. usability and acceptability), including an evaluation of AR glasses superiority in that regard.

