#### Potential efficacy of Reality DTx^®^

The study parameters to evaluate potential efficacy of the Reality DTx^®^ intervention will be subjected to a 2 × 3 mixed ANOVA with the within-subject factor Time (three levels: t0, t1, and t2) and the between-subjects factor Group (two levels: HoloLens 2, Magic Leap 2). The assumption of sphericity will be checked according to Girden [56]. If Greenhouse–Geisser’s epsilon exceeds 0.75, the Huynh–Feldt correction will be applied; otherwise, the Greenhouse–Geisser correction will be used. Effect sizes will be quantified with $${{\eta }_{p}}^{2}$$.

Paired-sample *t*-tests will be used for post hoc comparisons of significant main and/or interaction effects involving the factor Time (or paired-sample Wilcoxon tests if data is not normally distributed according to the Shapiro–Wilk test). We expect no main effect of Group, nor a Time by Group interaction, but only a main effect of Time, with superior performance after the Reality DTx^®^ intervention (t2) than before (t0, t1). In case t1 differs significantly from t0 as well (which may suggest learning/habituation in repeated test performance), an additional test on difference scores will then be performed to compare the magnitudes of intervention (t2–t1) and learning/habituation (t1–t0) effects with a paired-samples *t*-test (or paired-samples Wilcoxon tests if data is not normally distributed according to the Shapiro–Wilk test). We expect that potential intervention effects will be greater in magnitude than potential learning/habitation effects.

Because this is a feasibility trial, these comparisons will also be evaluated with Bayesian hypothesis testing [57, 58] using JASP [55], quantifying how much more likely the data support the alternative hypothesis (gait-and-balance outcomes differ over Time or Groups) compared to the null-hypothesis (gait-and-balance outcomes do not differ over Time or Groups), reported as the Bayes factor BF_10_ (alternative/null). In line with Jeffreys [57], we regard BF_10_-values between 1 and 3 as anecdotal evidence, values between 3 and 10 as moderate evidence, and values above 10 as strong evidence for the alternative hypotheses.

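### The waitlist comparison of t2–t1 with t1–t0 is posed without condition under Trial design, but is tested only if t1 differs significantly from t0

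*Protocol article*

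**What the plan says.** Under Trial design, the three visits serve to compare "intervention effects against usual care (i.e. does t2–t1 differ from t1–t0". A second, separate purpose is "controlling for potential learning effects in outcomes over repeated measurements (i.e. does t1–t0 systematically deviate from 0". Neither question depends on the answer to the other.

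Under Potential efficacy, the model is a "2 × 3 mixed ANOVA with the within-subject factor Time (three levels: t0, t1, and t2" and a Group factor for the glasses. Paired tests follow if an effect involving Time is significant. The expected finding is "only a main effect of Time, with superior performance after the Reality DTx^®^ intervention (t2) than before (t0, t1". The next step is conditional: "In case t1 differs significantly from t0 as well (which may suggest learning/habituation in repeated test performance), an additional test on difference scores" is to "compare the magnitudes of intervention (t2–t1) and learning/habituation (t1–t0) effects with a paired-samples" test or its Wilcoxon counterpart. The Bayesian paragraph says "these comparisons will also be evaluated with Bayesian hypothesis testing", with hypotheses about differences over Time or Groups. It adds no difference-score test outside the condition.

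**The concern.** Every participant receives the intervention, so the waitlist interval is the trial's only usual-care control. As written, that control enters the efficacy analysis in some data sets and not in others, depending on a significance test in 24 people. Where the test is skipped, the design question goes unanswered and an improvement from t1 to t2 has nothing set against it. Where it is run, it is run on data selected for a large t1–t0 change.

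Potential efficacy is part of the primary objective. The article also says that the three sets of scores will indicate obtainable effect sizes and help to size later randomised trials. An effect that contains uncorrected drift would mis-size them.

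**Working it through.** **Inputs from the Sample size section.** n = 24; target 1.63 s on the Timed Up-and-Go; SD over repeated measurements 2.0 s; one-tailed 5%; 95% power; required N = 18.

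**Assumptions, not in the document.** The 2.0 s is the SD of one change between two visits. Visit errors are independent with equal variance, so successive changes correlate at r = −0.5. Tests are two-sided at 5%. Practice sizes are as listed below.

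**The plan's own figure.** d = 1.63/2.0 = 0.815. The exact paired t-test, one-tailed 5%, gives power 0.953 at N = 18. The stated 18 is reproduced, and this supports reading 2.0 s as the SD of one change.

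**How weak the condition is.** The largest non-significant mean t1–t0 change is t(0.975, 23 df) × 2.0/√24 = 2.069 × 0.408 = 0.84 s. That is about half the target (0.84/1.63 = 0.52).

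**Simulated sequence.** 40,000 trials per setting, 12 per glasses group. The steps are the Time F-test, then the paired tests, then the difference-score test only if t1 versus t0 is significant. A false claim means t2 significantly better than t1, with no intervention effect and with the difference-score test either skipped or favourable. The comparator is the difference-score test always run.

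| Practice t0→t1, then t1→t2 | False claims, plan | Always run |
|---|---|---|
| 0.4 s, 0.4 s | 12% | 2.5% |
| 0.6 s, 0.6 s | 24% | 2.5% |
| 0.8 s, 0.8 s | 32% | 2.5% |
| 1.0 s, 1.0 s | 29% | 2.5% |
| second half the first (first 0.6–1.2 s) | about 8–12.5% | under 1% |
| none, or complete by t1 | 1.3–1.9% | at most 2.5% |

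In the four equal-gain rows, t1–t0 is significant in about 15, 29, 47 and 65% of trials. Nearly all the false claims arise where the test is skipped. The rate falls again for large practice (4.6% at 1.63 s per visit), because the condition is then almost always met.

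**When the test is triggered.** The contrast is (t2–t1) − (t1–t0) = t2 − 2·t1 + t0. A chance error at t1 that enlarges t1–t0 shrinks t2–t1, so selecting on a large waitlist gain pulls the contrast down. With practice of 0.6 s per visit and a true effect of 1.63 s, triggered tests average about 0.94 s with 22% power. Always run, the contrast averages 1.63 s with 60% power.

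**Precision of the contrast.** SD = 2.0 × √(2 − 2r). For 1.63 s at n = 24:

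| r | SD | d | Power, two-sided (one-sided) | N for 95%, two-sided (one-sided) |
|---|---|---|---|---|
| −0.5 | 3.46 s | 0.47 | 60% (72%) | 61 (51) |
| 0 | 2.83 s | 0.58 | 77% (86%) | 42 (34) |
| +0.25 | 2.45 s | 0.67 | 88% (94%) | 32 (26) |

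**When practice decelerates.** For a true 1.63 s effect the contrast averages 1.63 + second gain − first gain. That is about 1.33 s (44% power) for 0.6 s then 0.3 s, about 1.04 s (29%) if 0.6 s is complete by t1, and about 0.63 s (13%) if 1.0 s is complete by t1. The first of these gives 1.63 + 0.3 − 0.6 = 1.33; the others agree to within simulation error.

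**The case against.** Several points on the other side stand.

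- A gain made between t0 and t1 is already contained in t1, so taking t1 as the reference removes it. A reader might infer that any practice effect missed by the t1–t0 test is credited to the intervention. For t2 versus t1 that does not follow: only drift after t1 is credited. The comparison of t2 with t0 does include the first gain.
- A reader might also infer that the plan is biased whichever way the condition falls. The document gives neither the size nor the time course of practice, and with none, or none after t1, false claims stay below 2.5%.
- The always-run contrast is unbiased only if drift is equal in both intervals. If learning slows, it over-subtracts, so it should not be the sole efficacy analysis.
- With no practice and a true 1.63 s effect, the plan finds t2 better than t1 in about 95% of trials, while the contrast reaches significance in 60%.
- The Bayes factor for t1 versus t0 would grade the evidence on learning more finely than a p-value. It does not lift the condition.
- This is a feasibility trial. Efficacy is exploratory, effectiveness is left to later trials, and no progression rule hangs on this test. Nor does the article say that a non-significant t1–t0 proves the effect free of learning.

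These points limit the size and consequence of the problem. They do not reconcile the two sections.

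**Conclusion.** The point holds in a limited form and should be fixed. The Trial design section asks "does t2–t1 differ from t1–t0" unconditionally, and the analysis section answers it only after a significant Time effect and a significant t1–t0 difference. Non-significance at n = 24 leaves room for a waitlist gain of about half the target effect.

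The harm depends on drift that continues after t1. Under equal gains of 0.4–1.0 s per visit, false claims are about 12–32% against 2.5%; under halving gains they are about 8–12.5%. There is no inflation if practice is nil or finished by t1. When a waitlist gain triggers the test, the contrast is biased against the intervention. All these sizes rest on the assumed practice patterns, on independent visit errors and on 2.0 s being the SD of one change. The contradiction between the sections rests on none of them.

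**What to change.** - In the efficacy analysis, delete the condition on t1 differing from t0. For every efficacy outcome, always report t2–t1, t1–t0 and their within-participant difference with 95% confidence intervals, plus the Bayes factor for the difference. Do not make these depend on the omnibus F-test or on t1–t0.
- Use the difference to answer the Trial design question. State that it assumes equal drift in the two intervals and is therefore conservative if practice decelerates.
- When informing the later trial, give t2–t1 and the difference together as a range of effect sizes.
- In the Sample size section, say that N = 18 at 95% power covers a single change. Under independent visit errors, the difference has about 60% two-sided (72% one-sided) power for 1.63 s at n = 24.

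The visits, data and test are already planned, so the cost is rewording in two sections. The price is a noisier contrast than t2–t1 alone (97% two-sided power for 1.63 s at n = 24) and a less favourable stated power.

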## Discussion

This is the first remotely prescribed and monitored, personalised home-based AR therapeutic exergaming intervention specifically designed for pwPD to address their gait-and-balance impairments. The primary objective is to assess its feasibility (is it safe, adherable, accepted, and usable?) and to explore its potential efficacy (does it improve gait-and-balance outcomes?). The secondary objective is to evaluate AR glasses’ superiority in those regards (does it matter which AR glasses are used for performing, monitoring, and prescribing gait-and-balance exergaming?).

### Improving gait-and-balance exergaming with AR

To date, research into exergaming in Parkinson’s rehabilitation almost primarily focused on interventions presented on so-called non-immersive devices (e.g. Xbox Kinect or Nintendo Wii) [22, 59–63]. In several recent reviews, non-immersive exergaming interventions were considered at least equivalent in effectiveness for improving gait and balance and strengthening the effects of traditional supervised physiotherapy when combined [59–62]. A recent systematic review on home-based exergaming interventions concluded that exergaming in a home setting is effective in improving balance, mobility, and gait outcomes. Moreover, adherence to home-based exergaming was high, operationalised in terms of observance, enjoyment, and number of dropouts [22]. Therapeutic exergaming thus has strong potential for improving gait and balance. This form of delivering exercise may be particularly well suited for pwPD given that they are less inclined to engage in exercise due to motor symptoms (e.g. cardinal symptoms affecting range of motion) as well as non-motor symptoms (e.g. apathy, fatigue, anxiety and fear of falling) that reduce physical activity [21, 64, 65].

In the proposed clinical feasibility study, immersive AR technology will for the first time be used to deliver interactive exergaming for improving gait and balance in pwPD. One obvious advantage of AR exergaming is that one can directly interact with the digital content (i.e. physically step onto a digital mole popping out a molehill visible on the floor in the real world): there is no separation between the real and the digital world, allowing for task-specific training of visuomotor control of gait and balance. This stands in stark contrast with non-immersive or VR exergaming technologies where the interaction between movements made in the real world and the presented digital content is typically indirect (i.e. one can position a visual-feedback representation of a step made in the real world towards a mole popping out a molehill displayed on a screen.: Because of this indirect visuomotor coupling, the required magnitude of movements made in the real world to position a digital visual-feedback representation on a digital target has to be learned. Considering the reliance on visual (augmented) feedback and attention for motor control in pwPD [66, 67], exergaming with direct interactions in immersive environments (in contrast to indirect interactions in non-immersive or VR environments) might enhance perceptual-motor learning by directing attention and vision to task-relevant digital objects in the real world, that might, akin to real-world objects, act as affordances (i.e. possibilities) for action [66, 68, 69].

### Safety of home-based AR exergaming

A key objective of clinical feasibility trials is to address safety and adverse events of novel interventions like the AR-supported gait-and-balance therapeutic exergaming intervention Reality DTx^®^. This is deemed especially important when the exergaming intervention is delivered in an unsupervised home setting in a high fall-risk population like ours. Although several systematic reviews have reported that non-immersive exergaming to train gait and balance in pwPD is safe for use in both rehabilitation and home settings [22, 59, 60, 62], some adverse events in pwPD have been reported with both non-immersive (a non-injurious fall in a home-based step training study [70]) and immersive exergaming interventions (eyestrain and minor motion sickness during a dancing intervention using Google Glass [71]). We do not expect many adverse effects in the form of eyestrain and motion sickness, which is quite common in VR but not or less so with AR, in the proposed feasibility study. That is, Reality DTx^®^ runs on state-of-the-art AR glasses, where interactive augmented-reality content naturally blends with the real world and is largely static in case of the proposed study [29, 30]. Nevertheless, safety of use of immersive AR exergaming in the home setting of pwPD is yet to be determined.

To maximise safety of the participants in the current clinical feasibility study, the following recommendations have been implemented: (1) assess safety by the researchers (one of which is a trained clinician) during the first two laboratory assessments as well as via weekly semi-structured telephone calls during the 6-week intervention, (2) provide instructions on safety of use of the gait-and-balance exergames during the first two laboratory assessments and the home visit prior to the 6-weeks of home-based AR gait-and-balance exergaming, and (3) to tailor and adjust the gait-and-balance exergames to the functional level of the participant using remotely monitored objective information about adherence and performance as well as subjective information from weekly semi-structured telephone calls [22, 24, 62, 72].

### Future steps after this feasibility trial

The results on feasibility and potential efficacy will identify methodological challenges for future randomised controlled trials [73] and form the basis for design choices (e.g. required sample size, primary outcome measures) regarding the effectiveness of home-based AR gait-and-balance interventions for pwPD. Specifically, the complementary selection of outcome measures, quantifying various aspects of gait and balance such as walking adaptability, dynamic balance, and strength, will give a comprehensive insight into the specific constructs tackled with Reality DTx^®^ exergaming while the scores from baseline, pre-intervention, and post-intervention assessments will provide indications of obtainable effect sizes. Together, this will inform about the most specific and sensitive outcome measures to demonstrate gait-and-balance effects with remotely monitored and prescribed home-based AR therapeutic exergaming.

Such future studies will contribute to solving a societally important problem: accessibility to treatment. PD is a growing disease, and the number of pwPD is expected to double in the next two decades. This will increase the burden on already understaffed care, resulting in longer waitlists and suboptimal treatment. Technology like Reality DTx^®^ to safely deliver effective treatment (partly) at home may help counter this doom scenario, allowing pwPD to complete personalised and monitored therapeutic gait-and-balance exercises of the right frequency, intensity, with high levels of repetition, type, and duration in the convenience of their own home (saving time, costs, and burden associated with travelling to the healthcare professional) and own time (exercising whenever they feel ready, taking into account fatigue, medication effects and matters of work, household, and family), while potentially saving the healthcare system time and costs (the same healthcare professional can treat more pwPD). Being able to remotely monitor adherence and performance of the gait-and-balance exercises is crucial to guard the quality of treatment and to personalise treatment frequency, intensity, type, and time. With the pwPD participating in this feasibility trial, we will evaluate safety, adherence, acceptability, and usability of such a new care model supported by AR technology while future randomised controlled trials should address its effect and cost-effectiveness.

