### Sample size

For the proposed study, in which Reality DTx^®^ therapeutic gait-and-balance exergaming will for the first time be used independently at home, we will include a convenience sample of 24 participants to evaluate its initial feasibility (safety, adherence, and user experience) and potential efficacy for improving gait and balance. This sample size fits this type of study and is logistically feasible given the associated number of laboratory visits (72), weekly telephone calls (120), and home visits (24) vis-à-vis the availability of the gait laboratory and personnel, project duration, and funding. In addition, a sample of 24 participants is sufficient to evaluate the potential efficacy of this exergaming intervention. That is, with 95% power, a one-tailed alpha error of 5% and an expected minimum improvement of 1.63 s on the Timed Up-and-Go test (i.e. smallest detectable difference [42], a sample size of 18 is required to detect an effect with an effect size of 0.815 (Cohen’s *d* statistic; SD over repeated measurements 2.0 s [43]). This a priori required sample size calculation for differences between two dependent means was calculated with G*Power 3.1.9.7.

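### An effect size taken from whichever gait-and-balance measure responds most in these 24 people would be biased upward, and the t2–t1 comparisons are tied to significance tests; the protocol guards against neither

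*Protocol article*

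**What the plan says.** Three parts of the protocol article bear on this.

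- **Discussion, Future steps after this feasibility trial.** The results will "form the basis for design choices (e.g. required sample size, primary outcome measures") for later randomised trials. The scores from t0, t1 and t2 "will provide indications of obtainable effect sizes". The paragraph closes: "Together, this will inform about the most specific and sensitive outcome measures to demonstrate gait-and-balance effects". It names walking adaptability, dynamic balance and strength as constructs of interest.
- **Statistical analysis, Potential efficacy.** Each outcome goes into a 2 × 3 mixed ANOVA, with partial eta squared as effect size. Paired tests "will be used for post hoc comparisons of significant main and/or interaction effects involving the factor Time". The test of t2–t1 against t1–t0 is added only where t1 also differs significantly from t0. Bayes factors accompany these comparisons.
- **Trial design.** Whether t2–t1 differs from t1–t0 is given as the question the three visits are there to answer, with no significance condition.

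The sample is fixed under Sample size: "we will include a convenience sample of 24 participants to evaluate its initial feasibility".

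**The concern.** Among several noisy estimates, the largest tends to be large partly by chance. Here the same 24 people would show which measure is most sensitive and how big an effect can be obtained, so chance error favouring a measure also enters its effect size. Making the t2–t1 comparison depend on a significant Time effect works in the same direction, because comparisons that get made come from data that already looked favourable.

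The efficacy data are meant to inform the design of a randomised trial. An inflated effect used at face value gives too small a sample. The conditional testing also means that the contrast the design was built for may never be estimated for some outcomes.

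**Working it through.** **1. The plan's own figure.** Sample size gives an "expected minimum improvement of 1.63 s on the Timed Up-and-Go test" and "SD over repeated measurements 2.0 s", so d = 1.63 / 2.0 = 0.815. For a one-sided 5% paired t-test, power is P(T > t₀.₉₅,ₙ₋₁), where T is noncentral t with noncentrality d√n. At n = 18 this is 95.3%, so the stated 18 reproduces; at n = 24 it is 98.7%. That calculation concerns one named test (Timed Up-and-Go) and is not in dispute.

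**2. Candidate measures.** Primary study parameter lists Mini-BESTest, Timed Up-and-Go, Lindop and four walkway measures (avoidance margins, success rates, stepping accuracy, walking speed): 7. Strength, named in Future steps, adds Five Times Sit to Stand: 8.

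**3. Noise in one estimate.** SE(d) ≈ √(1/n + d²/2n). With n = 24:
- d = 0.3: √(0.0417 + 0.0019) = 0.21
- d = 0.5: √(0.0417 + 0.0052) = 0.22
- d = 0.815: √(0.0417 + 0.0138) = 0.24

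**4. Choosing the largest.** Simulation, 20,000 replicates, n = 24, complete data, normal changes, correlation 0.3 to 0.7 between measures. The documents give neither correlations nor true effects for most measures, so both are assumptions. The ratio is mean observed d of the selected measure divided by the mean of its own true d.

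Equal true effects:

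| True d | Selected d, 7 measures | Ratio, 7 measures | Ratio, 8 measures |
|---|---|---|---|
| 0.3 | 0.57 to 0.48 | 1.89 to 1.61 | 1.95 to 1.64 |
| 0.5 | 0.79 to 0.70 | 1.59 to 1.40 | 1.62 to 1.42 |
| 0.815 | 1.16 to 1.06 | 1.42 to 1.30 | 1.45 to 1.31 |

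(First value at correlation 0.3, second at 0.7.)

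True effects drawn from a normal distribution with SD 0.2 across measures:

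| Mean true d | Ratio, 7 measures | Ratio, 8 measures |
|---|---|---|
| 0.3 | 1.40 to 1.21 | 1.41 to 1.22 |
| 0.5 | 1.33 to 1.19 | 1.35 to 1.19 |

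With a single prespecified measure the ratio is 1.03 to 1.04, so selection causes nearly all of the bias.

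**5. The significance condition alone.** One measure, three visits, sphericity, no change from t0 to t1, Group factor ignored; t2–t1 is averaged over replicates with Time p < 0.05. A true 0.3 becomes 0.51, 0.5 becomes 0.61, and 0.815 becomes 0.85 (0.84 without the condition). The condition matters for small effects and hardly at all at the protocol's planning value.

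**6. What a ratio r would mean for a later trial.** Assume 80% power, two-sided 5%, and a between-arm standardised difference equal to the standardised change. Required n varies as 1/d², so the planned size is 1/r² of what is needed, and power at the true effect is about Φ(2.80/r − 1.96).

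| r | Planned n as share of needed | Power at the true effect |
|---|---|---|
| 1.2 | 1/1.44 = 69% | Φ(0.37) ≈ 65% |
| 1.3 | 1/1.69 = 59% | Φ(0.19) ≈ 58% |
| 1.4 | 1/1.96 = 51% | Φ(0.04) ≈ 52% |
| 1.95 | 1/3.80 = 26% | Φ(−0.52) ≈ 30% |

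Example: true 0.5, selected 0.75. Needed per arm: 2 × 2.80² / 0.5² ≈ 63. Planned: 2 × 2.80² / 0.75² ≈ 28. Power with 28 per arm is about 46%.

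**The case against.** The strongest reply is that the protocol fixes no rule for choosing the next trial's outcome. The wording is in the Discussion and is soft: it speaks of indications and of informing. Specificity is named beside sensitivity, and the t0 and t1 scores carry repeatability information. Choosing and sizing a later trial belongs to that trial's protocol. This stands. A reader might infer that the next trial will be undersized, or will probably fail; the documents do not support that, because they do not say the largest effect will be picked or used unadjusted.

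A reader might also count all the secondary scales as candidates, making 14. Future steps speaks of gait-and-balance effects and names adaptability, balance and strength, so 7 to 8 is the defensible number. Equal true effects are likewise an unfavourable case, since the protocol expects constructs to respond differently; hence the lower range above.

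Finally, partial eta squared carries no stated significance condition, and anonymised data are to be published or made available, so the changes could be recovered. That is partly right. But partial eta squared for Time summarises three visits and is not the t2–t1 change, and choosing the largest one would carry the same kind of selection bias. A Bayes factor weighs evidence and does not estimate the change.

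**Conclusion.** The point holds conditionally. The protocol states two uses of the same 24 people's scores that together invite selection bias, and it states no safeguard. If the most responsive measure's effect were carried forward unadjusted, the expected inflation is about 1.2 to 1.4 times when true effects differ (mean 0.3 to 0.5, SD 0.2, correlation 0.3 to 0.7) and about 1.3 to 1.95 times when they are equal (0.3 to 0.815). The direction was the same in every setting tried; the size depends on inputs the documents do not give.

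Separately, and without any assumption, the analysis section makes conditional a comparison that Trial design presents as the main question. Those two sections should be reconciled. The bias from the significance condition is secondary: noticeable at a true 0.3, negligible at 0.815.

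**What to change.** 1. **Statistical analysis, Potential efficacy.** For every efficacy outcome, whatever the ANOVA result, estimate the mean changes t2–t1 and t1–t0 and their difference, each with a 95% confidence interval. The tests can remain as a supplement.
2. **Discussion, Future steps.** Add a sentence saying that the effect observed for an outcome chosen for its response is inflated by selection and will not be used unadjusted to size a trial. One way to give this substance: use this trial for the SD of change, repeatability between t0 and t1, and completeness, and take the target difference from a prespecified important difference or a lower confidence limit.

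This protocol need not bind the later trial to a particular outcome or sizing rule; that remains open to debate.

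Cost: one extra table and a few sentences, with no new data. The drawback is that the effect size carried forward will look less favourable.
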